#### 9.2.2 Secondary endpoints

The following endpoints will be observed at all on-study scheduled evaluation days (section 6.1).

- 9.2.2.1 Change in CD4+ T-Cell count/mL in PBMC from baseline values.
- 9.2.2.2 Change in CD8+ T-Cell count/mL in PBMC from baseline values.
- 9.2.2.3 Total HIV-specific lymphocyte count and percent (CD3+ T-cells) based on a flow cytometric assay to detect antigen-specific IFN-gamma-producing cells that respond to whole Zn-finger-inactivated virus stimulation: To measure changes in the magnitude of HIV-specific CD3+ immune responses in the blood induced by vaccination.
- 9.2.2.4. HIV-specific CD8+ T-cell count and percent (CD3+/CD8+) based on a flow cytometric assay to detect antigen-specific IFN-gamma-producing cells that respond to whole Zn-finger-inactivated virus stimulation:  
To measure changes in the magnitude of HIV-specific CD8+ immune responses in the blood induced by vaccination.
- 9.2.2.5. Tolerability: occurrence of premature study treatment discontinuation (i.e. less than three hours of patch application at all designated sites) due to subject/parent/guardian/physician requesting discontinuation even though no protocol-defined toxicity endpoint had been reached (e.g. grade 1 or 2 toxicity or refuses rechallenge for higher grade, if appropriate.)
- 9.2.2.5. To evaluate if anti-DNA antibody responses develop after immunization.
- 9.2.2.6 Whether HIV-1 RNA copies/mL is below 50 or not.

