### 1.2 Secondary Objectives

- 1.2.1. To explore the immunogenicity of a LC002 for the treatment of individuals with chronic HIV-1 infection and HAART-induced durable suppression of viral replication.

- 1.2.1.1. To evaluate CD4+ and CD8+ T cell counts

- 1.2.1.2. To describe the distribution of HIV-specific immune responses with the following assays:

- Total HIV-specific lymphocyte count (CD3+ T-cells) using flow cytometric assay to detect antigen-specific IFN-gamma-producing cells that respond to whole Zn-finger-inactivated virus stimulation.
- HIV-specific CD8+ T cell count (CD8+, CD3+) using flow cytometric assay to detect antigen-specific IFN-gamma-producing cells that respond to whole Zn-finger-inactivated virus stimulation (1).

- 1.2.1.3. To explore whether LC002 treatment augments the magnitude of HIV-1 specific T-cell responses.

- 1.2.1.4 To explore whether increasing the dose of LC002 has greater efficacy in augmenting HIV specific T-cell responses in HIV-1 infected subjects.

- 1.2.1.5 To explore whether there are differences in longitudinal profiles of HIV-specific T-cell levels (and changes in T-cell levels from baseline) between treatment arms.

- 1.2.2. To monitor anti-DNA antibody response after immunization

- 1.2.3. To explore whether there are differences in the tolerability of LC002 with respect to pre-mature treatment discontinuation between treatment arms.
- 1.2.4. To explore if immunization results in any changes in viral load.

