## 8.0 CRITERIA FOR TREATMENT DISCONTINUATION

- Vaccine-related toxicity (see section 7.0 Toxicity Management).
- Requirement of prohibited concomitant medications (see section 5.4)
- Failure by the subject to attend 2 consecutive clinic visits.
- Pregnancy or breast-feeding.
- Request by the subject to withdraw.
- Request of the primary care provider if s/he thinks the study is no longer in the best interest of the subject.
- Subject judged by the investigator to be at significant risk of failing to comply with the provisions of the protocol as to cause harm to self or seriously interfere with the validity of the study results.
- At the discretion of the investigator or sponsor.

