#### 9.1.1 Primary Objectives

To evaluate the safety and tolerability of three different doses of LC002 in HIV-infected patients on HAART.

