### 9.2 Endpoints

#### 9.2.1 Primary endpoint: Safety

Occurrence of at least one grade 3 or higher adverse event including signs/symptoms, lab toxicities and clinical events that is "possibly, probably," or "definitely" related to study treatment (as judged by the Principal Investigator, including site clinicians on the team) any time from the first day of study treatment until 28 days after LC002 administration.

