### 9.3 Accrual

Any subject who withdraws from the study prematurely without experiencing a primary safety endpoint before Week 4 evaluation, and whose reasons for withdrawing from the study are unrelated to any real or perceived effect of the study vaccination or its administration, will be replaced with a subject assigned to the same dose cohort and the same arm. If possible, all subjects who discontinue the study prematurely will be followed for 48 weeks for study treatment safety information. A maximum of two subjects per cohort will be replaced.

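### The tolerability endpoint in 9.2.2.5 closes at patch removal, so no named endpoint counts a later withdrawal over a Grade 1-2 vaccine reaction

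*Protocol*

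**What the plan says.** Tolerability appears three times among the Protocol's aims. Objective 1.2.3 reads "To explore whether there are differences in the tolerability of LC002 with respect to pre-mature treatment discontinuation between treatment arms". Section 9.1 says the trial is meant to choose a regimen that subjects tolerate. Section 9.1.1 restates the primary objective as "To evaluate the safety and tolerability of three different doses of LC002 in HIV-infected patients on HAART".

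The only endpoint labelled tolerability is in 9.2.2.5 (a number also given to the anti-DNA antibody item): "occurrence of premature study treatment discontinuation (i.e. less than three hours of patch application at all designated sites". The sentence goes on to require that the subject, a parent or guardian, or a physician asked to stop "even though no protocol-defined toxicity endpoint had been reached (e.g. grade 1 or 2 toxicity or refuses rechallenge for higher grade, if appropriate".

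The provisions around it are:

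- **Sections 3.0 and 5.1.2:** there is one immunization, and the patch is removed at the site after three hours.
- **Sections 6.0 and 6.3.7:** the vaccine site is first evaluated just after patch removal, then on Days 7, 14 and 28.
- **Section 9.2.1:** the primary endpoint is "Occurrence of at least one grade 3 or higher adverse event", judged at least possibly related, up to 28 days after administration.
- **Section 9.3:** a subject who withdraws before Week 4 without a primary event is replaced only if the subject is one "whose reasons for withdrawing from the study are unrelated to any real or perceived effect of the study vaccination or its administration".
- **Section 8.0:** "Request by the subject to withdraw" is listed among the criteria for treatment discontinuation, with no time limit.

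**The concern.** Treatment here is a single three-hour application. An endpoint equated with an application shorter than three hours can therefore occur only while the patch is on. Local skin reactions to a topical vaccine can be seen, and can trouble a subject, in the days that follow, and every scheduled site evaluation falls after the endpoint has closed.

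The wording also does not fit this design. Refusing rechallenge presupposes a further dose, and none is planned. The lead-in to 9.2.2 has the secondary endpoints observed at all scheduled on-study days, which cannot apply to an event confined to Day 0.

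What is at stake is the tolerability result itself. A cohort could report no tolerability failures and no primary events even though a subject left because of a vaccine reaction.

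**Working it through.** The Protocol states no figure on this point, so there is none to reproduce. The check follows one case through the endpoints: the patch is worn for the full three hours, a Grade 2 itchy local reaction develops (Table 1 in 7.1.1), and the subject withdraws on Day 5 because of it.

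| Provision | What it needs | Does it count this subject? |
|---|---|---|
| 9.2.1 primary | related event, Grade 3 or higher | No, Grade 2 |
| 9.2.2.5 tolerability | under three hours of patch wear | No, three hours completed |
| Other 9.2.2 items | CD4+ and CD8+ counts, HIV-specific T cells, anti-DNA antibody, HIV-1 RNA | No, none concerns withdrawal or a low-grade reaction |
| 9.3 replacement | reason unrelated to vaccination | Not replaced, and not counted as an event |

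The result does not depend on how the phrase about all designated sites is read. Whether every site or only one must fall short, nothing can happen after removal.

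**Window.** 3 h / (28 × 24 h) = 3/672 = 0.45% of the time to Day 28. This is a share of time, not a share of events missed.

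**Counts.** One such subject in a cohort of three gives tolerability 0/3 and primary 0/3, while vaccine-related withdrawal is 1/3 = 33%. If all nine subjects left this way, both endpoints would still read 0/9.

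**Chance of seeing the case.** The Protocol gives no probability p of such a withdrawal, so p is assumed over 5% to 50%, with subjects independent. P(at least one of n) = 1 − (1 − p)^n.

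| Assumed p | At least 1 of 3 | At least 1 of 9 |
|---|---|---|
| 5% | 14.3% | 37.0% |
| 10% | 27.1% | 61.3% |
| 20% | 48.8% | 86.6% |
| 30% | 65.7% | 96.0% |
| 50% | 87.5% | 99.8% |

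**Escalation.** Section 4.3.1 wants all three subjects on study through Day 14; section 9.1.3 wants at least two. Suppose there is no primary event and all such withdrawals fall before Day 14. The on-study condition is then met with probability (1 − p)^3 under 4.3.1, and (1 − p)^3 + 3p(1 − p)^2 under 9.1.3.

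| Assumed p | 4.3.1 | 9.1.3 |
|---|---|---|
| 5% | 85.7% | 99.3% |
| 10% | 72.9% | 97.2% |
| 20% | 51.2% | 89.6% |
| 30% | 34.3% | 78.4% |
| 50% | 12.5% | 50.0% |

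A single early withdrawal fails the condition in 4.3.1 and passes the one in 9.1.3. The two sections must be reconciled.

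**The case against.** The strongest reply is that the endpoint matches its objective. Objective 1.2.3 speaks of premature treatment discontinuation, the treatment is one application, and 9.2.2.5 asks whether that application was completed. On this view, withdrawal from the study is a different quantity. The reply has force against 1.2.3 taken alone. It does not meet 9.1 and 9.1.1, which give the trial a broader tolerability aim with no other tolerability endpoint behind it. It also does not explain the rechallenge wording.

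The second reply is that the information is not lost, and this stands. Section 6.3.6 requires all grades of local reaction on the CRF. Section 9.3 seeks 48 weeks of safety follow-up, where possible, for those who leave early, and a vaccine-related leaver stays in the cohort unreplaced. Withdrawal before Day 14 also bears on escalation. That covers only part of the gap: it does not reach cohort 3, withdrawals after Day 14, or a single withdrawal under 9.1.3. A statistical analysis plan could list withdrawals by reason, but the Protocol itself fixes the endpoint definition.

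A reader might infer two stronger points, and neither is supported:

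- **That the choice of regimen rests on a biased count.** No section makes the 9.2.2.5 count a criterion for dose selection. Escalation turns on the primary safety endpoint and Day 14 retention.
- **That leaving Grade 3 patch removals out of the tolerability count is a defect.** A related Grade 3 reaction is already a primary endpoint event, so nothing is lost.

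**Conclusion.** The point holds as an endpoint gap. As defined, tolerability cannot register a subject who completes the single application and then withdraws before Week 4 over a Grade 1-2 vaccine reaction, and no other named endpoint counts that withdrawal. In a cohort of three, one such subject turns a vaccine-related withdrawal of 1/3 into a reported 0/3.

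The conclusion rests on the definition and needs no assumed rate; the probabilities above only show scale. It assumes that the reaction is graded 1 or 2 and that the three-hour clause is a definition and not an example, which is how the text puts it. The documents do not show that such withdrawals are likely. In an exploratory trial of nine subjects the consequence is confined to the reported tolerability result.

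**What to change.** Reword the tolerability item in 9.2.2.5 so that two components are reported separately for each cohort:

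1. patch application ended before three hours at the request of the subject or physician;
2. withdrawal from the study before the Week 4 evaluation because of a real or perceived effect of the vaccination or of its administration.

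Delete the rechallenge clause. Separately, reconcile the Day 14 on-study conditions in 4.3.1 and 9.1.3.

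The cost is a change of wording. Applying the replacement rule in 9.3 already requires the reason for withdrawal to be classified in this way, so no new visit or data item is needed. The downside for the sponsor is that the tolerability figure may look slightly less favourable.

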## 5.0 STUDY TREATMENT

### 5.1 Regimens, Administration, and Duration

Study treatment is DermaVir.

5.1.1 Subjects who meet the inclusion criteria will be sequentially enrolled into each cohort:

- Cohort 1:
  - Three subjects will receive a single low-dose vaccination (0.1 mg DNA/subject, 0.8 mL total, administered over two skin sites of 80 cm^2 each, 0.4 mL/site) at study day 0.
- Cohort 2:
  - Three subjects will receive a medium-dose vaccination (0.4 mg DNA/subject, 3.2 mL total, administered over four skin sites of 80 cm^2 each, 0.8 mL/site) at study day 0.
- Cohort 3:
  - Three subjects will receive a high-dose vaccination (0.8 mg DNA/subject, 6.4 mL total, administered over eight skin sites of 80 cm^2 each, 0.8 mL/site) at study day 0.

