  - Cohort 2 - Medium-dose vaccination: For each site, draw 0.8 ml of LC002 from one vial into the syringe.
  - Cohort 3 - High-dose vaccination: For each site, draw 0.8 ml of LC002 from one vial into the syringe.

**Note:** Discard needle into a sharps container before proceeding to next step.

11. Carefully insert the 1ml-syringe (without needle), via the open corner formed by (A), into the pocket formed by the patch, so that the tip reaches the lower third of the pocket.
12. Slowly expel the DermaVir formulation into the pocket, and withdraw the syringe.
13. Remove (A) and close the pocket completely by sealing the upper edges of the patch, and check that all edges of the patch adhere well and are sealed.
14. Repeat this procedure for all remaining skin sites.  
**Note:** Use a new syringe and needle to draw DermaVir for each site.
15. The skin patch will be removed after 3 hours **at the clinical site** by the investigator. Patches may be discarded with general waste but must be kept safely out of reach of children or animals.  
**Note:** The investigator will evaluate local reactogenicity immediately after removal of the patch.
16. After removal of the skin patch, all treated sites are to be washed with clean water.

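### The tolerability endpoint does not say whether a patch removed early at one site, or only at every site, makes an event, and the two readings move in opposite directions as sites rise from 2 to 4 to 8

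*Protocol*

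**What the plan says.** The tolerability item in Protocol section 9.2.2 (the first of two numbered 9.2.2.5) counts premature discontinuation of study treatment and explains it in a parenthesis as "less than three hours of patch application at all designated sites". A second condition concerns the reason: the subject, parent, guardian or physician must be "requesting discontinuation even though no protocol-defined toxicity endpoint had been reached".

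Objective 1.2.3 uses this endpoint to explore "differences in the tolerability of LC002 with respect to pre-mature treatment discontinuation between treatment arms". The trial has three dose cohorts and no other arms, so this is a comparison between cohorts.

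The cohorts differ in number of sites (section 5.1.1):
- Cohort 1: "administered over two skin sites of 80 cm 2 each, 0.4 mL/site"
- Cohort 2: "administered over four skin sites of 80 cm 2 each, 0.8 mL/site"
- Cohort 3: "administered over eight skin sites of 80 cm 2 each, 0.8 mL/site"

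In section 5.1.2 each site is prepared, patched and filled separately; step 14 reads "Repeat this procedure for all remaining skin sites". On duration, step 15 says "The skin patch will be removed after 3 hours". The same section requires every administration step to be documented on the CRF.

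**The concern.** The parenthesis supports two rules that classify the same subject in opposite ways:

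- **Every site short.** The event needs less than three hours at each designated site. Early removal at only some sites is not counted.
- **Any site short.** Full treatment is three hours at all designated sites, and anything less is premature. One early removal is enough.

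Because each site has its own patch, removal at only some sites is possible, and the protocol has no rule for it elsewhere. The number of sites rises with dose, so the choice of rule bears directly on objective 1.2.3. If the choice is left until the data are in, the description of tolerability by dose could depend on it. With three subjects per cohort, reclassifying one subject moves a cohort's rate by 1/3, or 33 percentage points.

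**Working it through.** The protocol states no expected rate, power or sample-size calculation for this endpoint, so there is no figure of its own to reproduce.

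**Inputs from the protocol.** Number of sites k = 2, 4, 8 (section 5.1.1). Volumes confirm the site counts: 2 × 0.4 = 0.8 mL, 4 × 0.8 = 3.2 mL, 8 × 0.8 = 6.4 mL, as stated there. Subjects per cohort = 3 (Schema and section 5.1.1).

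**Assumed inputs.** Probability p that a given site has its patch removed before three hours on a request that meets the endpoint's second condition: 0.10, with a range of 0.05 to 0.30. Correlation ρ between sites within a subject: 0, 0.5, 0.8 and 1. Neither p nor ρ is in the protocol.

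**Independent sites (ρ = 0).**
- Every site short: p^k
- Any site short: 1 − (1 − p)^k

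At p = 0.10:
- Every site: 0.1² = 0.01; 0.1⁴ = 0.0001; 0.1⁸ = 0.00000001
- Any site: 1 − 0.9² = 0.190; 1 − 0.9⁴ = 0.344; 1 − 0.9⁸ = 0.570
- Partial removals, counted by one rule and not by the other (the difference): 0.180, 0.344, 0.570
- At least one event among 3 subjects under any site: 0.47, 0.72, 0.92

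Over p = 0.05 to 0.30, any site gives 0.098–0.510 (2 sites), 0.185–0.760 (4) and 0.337–0.942 (8).

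**Correlated sites.** Beta-binomial with a = p(1/ρ − 1) and b = (1 − p)(1/ρ − 1):
- Every site short: B(a + k, b) / B(a, b)
- Any site short: 1 − B(a, b + k) / B(a, b)

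For ρ = 0.5 and p = 0.10, a = 0.1 and b = 0.9. With two sites, every site = (0.1 × 1.1)/(1 × 2) = 0.055, and any site = 1 − (0.9 × 1.9)/(1 × 2) = 0.145.

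Per-subject event probability at p = 0.10:

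| ρ | Every site short: 2 / 4 / 8 sites | Any site short: 2 / 4 / 8 sites |
|---|---|---|
| 0 | 0.010 / 0.0001 / 0.00000001 | 0.190 / 0.344 / 0.570 |
| 0.5 | 0.055 / 0.030 / 0.016 | 0.145 / 0.194 / 0.244 |
| 0.8 | 0.082 / 0.069 / 0.058 | 0.118 / 0.135 / 0.150 |
| 1 (all patches or none) | 0.10 / 0.10 / 0.10 | 0.10 / 0.10 / 0.10 |

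The gradients run in opposite directions at every ρ below 1. They shrink as ρ rises and vanish at ρ = 1.

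**What counts as a site in cohort 3.** Section 5.1.1, the site table in section 5.1.2 and the composition table in section 5.2.3 give eight single sites of 80 cm². Step 3 of section 5.1.2 has two patches side by side at each cohort 3 site, while step 9 has one patch per site. The kit list says each patch covers 80 cm². Eight sites with two patches each would be 16 × 80 = 1,280 cm², against 8 × 80 = 640 cm². The unit being counted is therefore also unsettled.

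**The case against.** A reader might infer that the endpoint as written counts only removal at every site, so that partial removals are certainly missed and the cohort comparison is certainly distorted. The documents do not support that. The parenthesis explains what is premature, and full treatment is three hours at every site. Read that way, anything less is an event and nothing is missed. This reading is equally open and may be the intended one. What stands is that the wording is indeterminate.

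The other objections, and what remains of them:

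- **The size is assumed.** Correct. No per-site rate is given, and independence is the extreme case. A request to discontinue is largely one person's decision, so patches may well come off together. The correlated rows above belong beside the independent one.
- **The number of sites is part of the dose.** Also correct. The dosing rationale in section 2.2 bases the dose on the skin area treated, and cohorts 2 and 3 have the same volume per site and differ only in the number of sites. More early removals with eight patches than with four would partly be a real property of the regimen. It would be wrong to call the whole gradient an artefact.
- **Changing *all* to *any* does not remove the dependence on site number.** True: 19%, 34% and 57% remain at p = 0.10 with independence. The rewording settles partial removals; only a per-site count separates the two effects.
- **Little depends on it.** Objective 1.2.3 is exploratory. Local reactions are graded separately (section 7.1.1), related grade 3 or higher events are in the primary endpoint (section 9.2.1), and the escalation rule (section 9.1.3) does not use this endpoint. That limits the severity. Still, section 9.1.1 names tolerability in the primary objective, and this is the only endpoint carrying that label.
- **A scoring rule could sit in the analysis plan.** That would answer an omission. Here the protocol states the definition itself and leaves two meanings in it.

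**Conclusion.** The point holds as an ambiguity. The definition admits two rules, no other section chooses between them, and they pull the cohort comparison in opposite directions unless subjects remove all patches or none. At an assumed 10% per site, the gap between the rules in the eight-site cohort is about 57 percentage points with independent sites, 24.4 − 1.6 = 22.8 points at correlation 0.5, and zero at correlation 1. These figures illustrate the mechanism and do not predict what the trial will show. Severity is minor: an exploratory secondary endpoint with three subjects per cohort that plays no part in dose escalation.

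**What to change.** 1. In the tolerability item of section 9.2.2, change *all* to *any* before the words designated site(s), so that less than three hours at one site is an event.
2. Report for each subject the number of sites removed early out of sites applied (2, 4 or 8), so that objective 1.2.3 can be described both per subject and per site.
3. Confirm that the CRF has a removal time for each site. Section 5.1.2 requires each administration step to be documented and removal is step 15, but a time per site is not expressly asked for.
4. Reconcile step 3 of section 5.1.2 (two patches per site in cohort 3) with step 9 and with the eight single 80 cm² sites given elsewhere, so that a designated site has one meaning. Which description is right is for the sponsor to settle.

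The cost is one word, one descriptive column, at most one CRF field, and a consistency correction to the administration text. Sample size and visits are unchanged.

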## 4.0 SELECTION AND ENROLLMENT OF SUBJECTS

### 4.1 Inclusion Criteria

- 4.1.1 Ability and willingness of subject or legal guardian/representative to give written informed consent.
- 4.1.2 HIV-1 infection, as documented by any licensed ELISA test kit and confirmed by Western blot, HIV-1 culture, HIV-1 antigen, plasma HIV-1 RNA, or a second antibody test by a method other than ELISA is acceptable as an alternative confirmatory test at any time prior to study entry.
- 4.1.3 On a stable antiretroviral regimen (containing drugs of at least two different classes) without changes or interruptions for at least 24 weeks prior to study entry.
- 4.1.4 Plasma HIV-1 RNA level of less than 50 copies/mL, while on a stable antiretroviral regimen, obtained at least twice within the 12 weeks prior to study entry.
- 4.1.5 Peak plasma HIV-1 RNA level before initiation of HAART > 1000 copies/mL.
- 4.1.6 CD4 cell count > 300 cells/mm^3 within the 12 weeks prior to study entry.
- 4.1.7 Nadir (lowest) CD4+ cell count > 250 cells/mm^3 at any time prior to study entry.
- 4.1.8 The following laboratory values, obtained within 30 days prior to study entry:
  - Absolute neutrophil count (ANC)  $\geq 1000/\text{mm}^3$
  - Hemoglobin  $\geq 9.0$  g/dL
  - Platelet count  $\geq 50,000/\text{mm}^3$
  - Serum creatinine  $\leq$  upper limit of the laboratory normal range (ULN)
  - AST (SGOT), ALT (SGPT), and alkaline phosphatase  $\leq 2.5 \times \text{ULN}$
  - Total bilirubin  $\leq 2.5 \times \text{ULN}$

- Anti-nuclear antibody (ANA) titer of 1:40 or lower and negative for serum anti-double-stranded DNA antibody (anti-ds-DNA) test result at screening.

- 4.1.9 All women of reproductive potential (who have not reached menopause or undergone hysterectomy, oophorectomy, or tubal ligation) must have a negative urine  $\beta$ -HCG pregnancy test performed within 14 days prior to study entry.

Female study volunteers who are not of reproductive potential (who have reached menopause or undergone hysterectomy, oophorectomy, or tubal ligation) or whose male partner has undergone successful vasectomy with documented azoospermia or has documented azoospermia for any other reason, are eligible without requiring the use of contraception. Acceptable documentation of menopause, sterilization, and azoospermia is written or oral documentation communicated by clinician or clinician's staff of one of the following:

- Physician report/letter

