### 3. Treatment-phase – evaluations from Day 0 to Day 28:

- a. Medication history at Days 0, 28.
- b. Targeted physical examination at Days 0, 7, 14, 28.
- c. Complete physical examination at Day 28.
- d. Vaccine local site evaluations at Days 0 (immediately after removal of skin patch), 7, 14, 28.
- e. Hematology evaluations at Days 0, 7, 14, 28.
- f. Blood chemistries and liver function tests at Days 0, 7, 14, 28.
- g. Autoantibodies (ANA, anti-ds-DNA) at Day 28.
- h. Urinalysis at Days 0, 7, 14, 28.
- i. Urine pregnancy test at Day 0.
- j. HIV-1 RNA at Days 0, 7, 28.
- k. CD4/CD8 count and CD45RA/RO at Days 0, 7, 14, 28.
- l. Virus-specific immune responses: samples at Days 0, 14, 28.
- m. Plasma and PBMCs for storage at Days 0, 7, 14, 28.

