### 4. Post-treatment phase – evaluations after Day 28 (safety follow up):

- a. Medication history at Weeks 12, 24, 36, 48.
- b. Targeted physical examination at Weeks 12, 24, and 36.
- c. Complete physical examination at Week 48.
- d. Hematology evaluations at Weeks 12, 24, 36 and 48.
- e. Blood chemistries and liver function tests at Weeks 12, 24, 36 and 48.
- f. Autoantibodies (ANA, anti-ds-DNA) at Week 48.
- g. Urinalysis at Weeks 12, 24, 36 and 48.
- h. HIV-1 RNA at Weeks 12, 24, 36 and 48.
- i. CD4/CD8 count at Weeks 12, 24, 36 and 48.

- j. Plasma and PBMCs for storage at Weeks 12, 24, 36 and 48.

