#### 6.3.16 Plasma HIV-1 RNA

The screening HIV-1 RNA must have been performed locally within three months of entry. Eligibility will be determined based on the screening value. The pre-entry HIV-1 RNA must be performed within 14 days prior to study entry. The baseline value will be the geometric mean of the pre-entry and entry determination. All tests will be performed locally.

Additional laboratory evaluations (not considered in the Division of AIDS Table for Grading Adult Adverse Experiences):

Red blood cell count (RBC), granulocytes, lymphocytes, monocytes, eosinophils, basophils, prothrombin time, creatinine, amylase, LDH, glucose, total protein, cholesterol and triglycerides, C-reactive protein, direct bilirubin, albumin.

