### 7.2 Antiretroviral Drugs

Unanticipated and anticipated toxicities from the HAART regimen will be graded according to the Division of AIDS Table for Grading Adult Adverse Experiences (see Appendix IV). Any Grade 3 or 4 toxicities that result in a temporary or permanent change in an antiretroviral therapy must be reported to the Principal Investigator.

Anticipated toxicities resulting from components of the HAART regimen will be managed by the subject's clinician according to best clinical practice including dose reductions when indicated.

If the HIV-1 viral load becomes detectable (plasma HIV-1 RNA > 1,000 copies/mL) either during the treatment phase (Day 0 to 28) or 48-week follow up, it should be repeated one week later and compliance issues should be ruled out. If the repeated HIV-1 viral load is detectable (plasma HIV-1 RNA > 1,000 copies/ml) genotyping should be performed and HAART changed if necessary.

In case of virologic failure, genotyping will also be performed on the nef gene. As the nef gene contained in the DNA of LC002 is truncated, detection of a truncated nef gene would indicate recombination of the patient's virus with the vaccine. All patients with virologic failure will be followed for the complete 48-week follow up period.

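### The only viral-load endpoint is a below-50 indicator, so it cannot describe the change in viral load that the objective asks about; keep it and add the quantitative result

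*Protocol*

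**What the plan says.** Four parts of the protocol bear on viral load as an outcome.

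- **Objective** (1.2 Secondary Objectives, item 1.2.4): "To explore if immunization results in any changes in viral load".
- **Baseline** (6.3.16 Plasma HIV-1 RNA): "The baseline value will be the geometric mean of the pre-entry and entry determination". A geometric mean is a mean on the log scale, so this baseline is built for a quantitative analysis.
- **Endpoint** (9.2.2 Secondary endpoints, item 9.2.2.6): "Whether HIV-1 RNA copies/mL is below 50 or not". No other viral-load endpoint is listed. In the same list, CD4+ cells are analysed as "Change in CD4+ T-Cell count/mL in PBMC from baseline values", and CD8+ cells likewise.
- **Management** (7.2 Antiretroviral Drugs): "If the HIV-1 viral load becomes detectable (plasma HIV-1 RNA > 1,000 copies/mL", the test is repeated a week later. If it is still above that level, genotyping follows. In virologic failure the nef gene is also genotyped, to look for recombination with the vaccine.

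Measurement is frequent. Section 6.0 lists "HIV-1 RNA at Days 0, 7, 28" for the treatment phase and "HIV-1 RNA at Weeks 12, 24, 36 and 48" for follow-up, which makes six results per subject after vaccination.

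Entry is restricted to suppressed subjects. Inclusion criterion 4.1.4 requires "Plasma HIV-1 RNA level of less than 50 copies/mL, while on a stable antiretroviral regimen", at least twice in the 12 weeks before entry. Exclusion 4.2.1 removes anyone above 50 in that window, and section 5.4.1 requires a regimen that suppresses below 50 on study.

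**The concern.** The objective and the endpoint do not match. The objective is about change of any kind, and the endpoint records only which side of 50 copies/mL a value falls on. The baseline in 6.3.16 enters no endpoint.

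For a plasmid that carries HIV genes, the size of any rise is the informative part of a viral-load result. A single low value just above 50 and a full rebound have different meanings, and section 7.2 already separates them for individual care. The endpoint does not carry that separation into what is reported. The repeat test in 7.2 is also not one of the scheduled evaluation days on which 9.2.2 says its endpoints are observed, so a confirmed value above 1,000 has no place in any endpoint.

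A second risk concerns the data. The Laboratory Evaluations text in section 6.3 requires post-baseline laboratory values on the CRF only from a given toxicity grade upward. The Appendix IV grading table has no row for HIV-1 RNA, only a general scale for unlisted abnormalities. The endpoint is then the main text that obliges viral-load data to reach the database, and it asks for a yes or no. This is an inference, since the CRF itself is not shown.

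**Working it through.** The protocol states no effect size, error rate or power for this endpoint, so there is no figure of its own to reproduce.

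**1. What the endpoint scores alike.** The change is log10(value / baseline), with the baseline set at 50 copies/mL for illustration.

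| Value (copies/mL) | Endpoint 9.2.2.6 | log10 change from 50 | Above 1,000 (7.2) |
|---|---|---|---|
| 51 | not below 50 | +0.01 | no |
| 60 | not below 50 | +0.08 | no |
| 200 | not below 50 | +0.60 | no |
| 1,001 | not below 50 | +1.30 | yes |
| 100,000 | not below 50 | +3.30 | yes |

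All five get one score. The first and last differ by log10(100,000 / 51) = 3.29.

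**2. How easily isolated low values fill the endpoint.** The documents give no rate of transient values at or above 50, so let q be an assumed rate per measurement, independent across measurements. The chance of at least one such result is 1 − (1 − q)^n, with n = 6 for one subject and n = 9 × 6 = 54 for the trial.

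| q | One subject | Any of 9 subjects |
|---|---|---|
| 1% | 5.9% | 41.9% |
| 2% | 11.4% | 66.4% |
| 5% | 26.5% | 93.7% |
| 10% | 46.9% | 99.7% |

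Some results of not below 50 are therefore plausible without any rebound. At a single visit the indicator cannot separate the two. The pattern over six visits separates them in part.

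**3. What a quantitative form would gain in a dose comparison.** The assumptions are illustrative: maximum post-vaccination log10 RNA is normal with SD 0.7, values are censored at log10(50) = 1.699, there are 3 subjects per dose, and the test is an exact one-sided 5% permutation trend test over the 9!/(3!·3!·3!) = 1,680 assignments. The expected number above 50 is 3 × Σ[1 − Φ((1.699 − mean) / 0.7)] over the three doses.

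| Mean log10 by dose | Expected number of 9 above 50 | Power, indicator | Power, censored log10 | Gain (points) |
|---|---|---|---|---|
| 1.2 / 1.7 / 2.2 | 4.5 | 18% | 34% | 16 |
| 1.5 / 2.0 / 2.5 | 5.8 | 16% | 40% | 24 |
| 1.5 / 2.2 / 3.0 | 6.4 | 21% | 69% | 48 |
| 1.7 / 2.7 / 3.7 | 7.3 | 12% | 90% | 78 |
| 0.5 / 0.75 / 1.0 | 0.9 | 0.2% | 0.8% | 0.6 |
| 0.5 / 0.8 / 1.2 | 1.1 | 1.2% | 2.5% | 1.3 |
| 0.8 / 1.0 / 1.3 | 1.6 | 1.8% | 4.0% | 2.2 |

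With equal means of 1.2, rejection is 0.7% for the indicator and 1.5% for the censored value, so both hold the 5% level. Simulation error is about a point or two in the upper rows. The large gains occur only where about half or more of the subjects lose suppression. In the 78-point row the exceedance rates are 50%, 92% and 99.8% by dose, which would be plain without a test. If nobody exceeds 50, the two forms are identical.

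**4. Why change from baseline cannot simply replace the indicator.** Baselines are expected to lie below 50. A result of 60 copies/mL is +0.08 if the baseline is taken as 50, since log10(60/50) = 0.08, and +0.38 if it is taken as 25, since log10(60/25) = 0.38. The answer depends on the rule for values under 50.

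**The case against.** The strongest defence is that 50 copies/mL is the protocol's own definition of suppression, used in criteria 4.1.4 and 4.2.1 and in section 5.4.1. Every subject is expected to start below it, so the first change that can be seen is loss of suppression, and the indicator records that. The CD4+ and CD8+ contrast is weaker than it looks, because those counts are not confined below a threshold at entry. Rules for values under the limit are commonly left to a statistical analysis plan, which is not shown. All of this stands. It justifies having the indicator, but not having it as the only endpoint for an objective about any change.

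Three stronger readings are tempting, and the documents do not support them.

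- *Rebound would go unnoticed.* Section 7.2 requires a repeat, genotyping and nef testing above 1,000 copies/mL, and 48-week follow-up of all virologic failures. The quantitative assay is run regardless, and nothing bars tabulating its results. The gap is in the defined outcome, not in individual care.
- *The cut removes most of the power to see a dose relation.* No trend test is planned, objective 1.2.4 is exploratory and asks about immunization rather than dose, and the large gains need widespread loss of suppression. The simulation also reduces each subject to one maximum, whereas 9.2.2 observes the endpoint at every scheduled visit.
- *The indicator should be replaced by change from baseline.* That would rest on a baseline expected to be below 50 in nearly everyone, and so on how such values are handled.

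**Conclusion.** The point holds in a limited form. Endpoint 9.2.2.6 does not measure what objective 1.2.4 asks, leaves the 6.3.16 baseline unused, and scores a low transient value and a full rebound alike. These follow from the text and need no assumption.

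The impact is modest. One exploratory secondary endpoint in 9 subjects is affected, and the primary safety endpoint (9.2.1) and the escalation rule (9.1.3) are not. The gain of 16 to 78 points applies only if about half or more of the subjects exceed 50. With 1 to 2 of 9 it is about 2 points or less, and with none it is zero. These figures rest on assumed means and an SD of 0.7. The case for change is therefore descriptive completeness at almost no cost, not power. That quantitative values might not reach the database is an inference from the CRF rules. That 50 is the assay's lower limit is also not stated.

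**What to change.** Keep the below-50 indicator and add to 9.2.2.6:

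- HIV-1 RNA in log10 copies/mL at each scheduled visit, and the maximum post-vaccination value per subject, listed by dose. Values under 50 are treated as left-censored, and tied at the limit in any rank method.
- Change from the 6.3.16 baseline, under the same rule for values below 50.
- The number of subjects with a value above 1,000 copies/mL, and the number in whom the repeat test is also above it. This takes the threshold of 7.2 only as a reporting category and changes nothing in management.

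State in section 6.3 that all quantitative HIV-1 RNA results, including unscheduled repeats, are entered on the CRF whatever their grade.

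The cost is wording, slightly more data entry and a few more listings. The assay already runs on Days 0, 7 and 28 and at Weeks 12, 24, 36 and 48, so no sample or visit is added.
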